### Screening

CHWs collect samples of vaginal flora and urine during home visits between 13 and 19 weeks gestation. Vaginal specimens are collected via sterile self-administered vaginal swabs. Self-administered vaginal swabs have been used with high acceptability and quality in diverse populations including in Bangladesh, providing cost-savings and cost effectiveness for STI testing [43–46]. Women are instructed by the CHW to insert a Dacron swab ~4–5 cm into the vagina, allow the swab to stand for 15 s, and rub the lateral walls of the vagina for 4–5 s prior to withdrawal [47]. The CHW gently rolls the swab onto a plain glass slide and allows it to air dry prior to transport to the Sylhet field laboratory. A clean catch midstream urine specimen is obtained for urine culture. The CHW instructs the mother to spread the labia widely before collecting 20–30 mL of the midstream urine into a sterile wide-mouthed container.

### Specimen storage and transport

All specimens collected in the field by CHWs are immediately labeled and stored in a cooler refrigerated with ice packs (~2–8 °C) and transported to the Sylhet field laboratory. In the field laboratory, the vaginal smears are Gram stained within 1–2 days of plating [22]. Urine specimens are inoculated on sheep blood agar plates in the Sylhet field laboratory within 6 h of collection for incubation.

### Diagnosis of abnormal vaginal flora

Abnormal vaginal flora are classified by microscopic examination of a Gram stained sample of the vaginal smear and Nugent scored (Table 1) [22]. Nugent scores between 7 and 10 are classified as BV, and scores between 4 and 6 are classified as intermediate flora; all scores ≥ 4 are classified as AVF [48]. The time window from specimen collection to Nugent scoring is 4 days, and from Nugent scoring to first dose of treatment is 2 days, for a total of 6 days from sample collection to treatment. Treatment is based on a single reading by a trained and standardized microbiologist. The laboratory staff are trained and standardized in Nugent scoring on a non-study sample of slides (*n* = 250) until there is high concordance of readings (kappa >0.8) between laboratory staff and gold standard scorers, and high sensitivity and specificity of AVF and BV compared to the gold standard reader (>85 %) prior to the initiation of the study.

**Table 1 Tab1:** Nugent scoring for vaginal flora

*Lactobacillus* Morphotypes^a^	*Gardnerella* / *Bacteroides* Morphotypes^a^	Curved gram-variable rods
Score 0 for >30	Score 0 for 0	Score 0 for 0
Score 1 for 15–30	Score 1 for <1	Score 1 for <5
Score 2 for 14	Score 2 for 1–4	Score 2 for 5+
Score 3 for <1	Score 3 for 5–30	
Score 4 for 0	Score 4 for >30	

^**a**^Average count per high powered field (1000× oil immersion), viewing at least 10–20 fields

### Diagnosis of urinary tract infection

Urine specimens are plated on standard MacConky and Blood agar plates and incubated for 48 h. Bacterial growth is speciated using standard microbial techniques, and antibiotic sensitivity patterns are determined. Bacterial growth is defined in the following categories: 1) ***high-burden urinary tract infection***: bactiuria of >10^5^ colony forming units (CFU) per 1 mL of urine of a single uropathogen [49], 2) ***intermediate growth***: bactiuria with >10^3^–10^5^ CFU/mL of a single uropathogen, and 3) ***contamination***: bacterial growth of >1 organism OR growth of a non-urinary tract pathogen. At the time of the specimen collection visit, CHWs inquire about maternal symptoms of UTI (dysuria, urinary frequency, hematuria, abdominal pain, fever, flank pain). ***Symptomatic intermediate growth*** is defined as mothers with intermediate burden growth and UTI symptoms. ***Cystitis*** is diagnosed in women with positive urine culture (high burden or intermediate growth) and symptoms of dysuria, urinary frequency, hematuria, urinary urgency or suprapubic tenderness, without upper urinary tract symptoms (fever, chills, flank or back pain) [49]. ***Pyelonephritis*** is diagnosed in women with positive urine culture and systemic symptoms (fever, chills, flank pain or back pain) [49].

### Treatment of abnormal vaginal flora and urinary tract infections

Women who are clinically symptomatic at any antenatal or postnatal visit are referred to the sub-district hospital for full evaluation and treatment (Fig. 3). Women with symptoms of illness are visited on the following day to follow her clinical status and ensure referral compliance. CHWs conduct a home visit to women with positive test results within 48 h of receiving the results to initiate treatment. AVF is treated with oral clindamycin 300 mg per oral (po) twice daily (bid) for 5 days per the regimen used by Ugwumadu [24]. After the initial treatment course, women are rescreened 3 weeks after the first treatment. If the second vaginal specimen has Nugent score ≥4, the women are retreated with a second course of clindamycin 300 mg po bid for 5 days. For retreated women, a final vaginal sample is collected 3 weeks after the second course of antibiotics to document response to treatment.

**Fig. 3 Fig3:**
[figure not shown]
Referral and treatment algorithm for intervention clusters

The algorithm for treatment of positive urine cultures is shown in Fig. 4. All mothers with high burden UTI and symptomatic intermediate growth are treated. The initial antibiotic treatment is Macrobid/Nitrofurantoin 100 mg po bid for 7 days. Women diagnosed with pyelonephritis are referred to the sub-district hospital for further evaluation and management. For all positive urine cultures, a repeat urine culture is obtained 1 week after completion of antibiotics for test of cure. If the second urine culture is positive, the supervising field physician selects an appropriate antibiotic based on the prior culture’s antimicrobial sensitivity pattern. Persistent UTIs are referred to Sylhet Osmani Medical College Hospital for evaluation and management.

**Fig. 4 Fig4:**
[figure not shown]
Urine culture treatment algorithm

### Point of care testing validation

On a subsample of women (*n* = 1386), point of care tests are conducted in the field site at the same time as the first specimen collection. An additional vaginal swab is taken for rapid testing with BVBLUE (Rapid Sialidase test, Genzyme, Cambridge, MA). An additional 2 mL aliquot of urine is tested with the URISCREEN test (rapid catalase screen, URISCREEN, Jant Pharmacal, Encino, CA).

### Medication adherence and monitoring

The VHWs and CHWs monitor all women who are prescribed medication for medication adherence and adverse events. The CHW observes the mother take the first antibiotic dose and provides her with a medication punch card to indicate every dose taken. The CHW visits the mother 2–3 days after starting the antibiotic to screen for symptoms of *C. difficile* diarrhea/colitis (associated with clindamycin) and hemolytic anemia (associated with Macrobid). At the end of the antibiotic course, the CHW collects the medication punch card, conducts a pill count, and assesses compliance and response to therapy based on the mother’s history.

### Post-natal visits

CHWs in both intervention and control clusters are notified of all births through a community-based notification system which relies on families and VHWs. During the first postnatal visit, the CHW records the date and outcome of delivery, including stillbirths (pregnancy losses ≥28 weeks) or late miscarriages (pregnancy losses 20 to <28 weeks). If a stillbirth has occurred, the CHW notifies a supervisory staff member who returns to conduct a verbal autopsy module for stillbirth [50]. For all births, CHWs record the vital status of mother and baby, and basic information regarding characteristics of labor and delivery, including data on timing and duration of labor, timing (before or after onset of labor) and length of rupture of membranes, maternal fever, and other morbidity before, during, and after delivery. For each live newborn delivered, the newborn's sex, weight, and care given during and immediately after birth (bathing, massage, cord care, breastfeeding practices) are recorded.

At the first postnatal visit, which occurs in most cases on the first day of life, CHWs weigh the infant with a digital weighing scale. At the start of the study, the KL-218 digital scale (precision 10 gm, Donghuan Electronic Manufacturing, Donghuan, China) was used. The scale was transitioned to the Tanita BD 585 digital pediatric scale in September 2015 (precision 10 gm, Tanita corporation, Toyota, Japan). Scales are calibrated daily prior to home visits. CHWs also measure head circumference, mid-upper arm circumference, infant length, and chest circumference. These measurements are repeated thrice (median value used for analysis). The general health status of the mother and infant are assessed by the CHW during postnatal visits. The mothers are assessed for vital status, fever, uterine tenderness and symptoms of postpartum hemorrhage. Women with symptoms of postpartum complications (fever >38.3 °C, abdominal/uterine tenderness, self-report of excessive hemorrhage) are referred to government sub-district hospitals for further management. Evaluation of the neonate is conducted according to an IMCI-type algorithm [51], and the CHW assesses the infant for temperature, respiratory rate, and signs and symptoms of severe illness. The CHWs conduct follow up postnatal visits at homes in which severe illness is detected in the mother or neonate within the next 24 h to monitor the mother/infant for signs of illness and reinforce the referral. If the ill mother/newborn has not sought hospital care, the CHW facilitates referral by helping to arrange transportation and payment of hospital fees. The CHW returns on days 3, 7, and 28 after birth to reassess and inquire about signs of morbidity in the mother and infant.

### Outcome measures

The primary and secondary study outcomes and definitions are shown in Table 2.

**Table 2 Tab2:** Study outcomes for MIST trial

	Numerator	Denominator
Primary outcome		
Preterm live birth	Live births <37 weeks of gestation	All live births
Secondary outcomes		
Preterm birth and late miscarriage	Live births (28 to <37 weeks)	All birth outcomes ≥ 20 weeks
	Stillbirth (28 to <37 weeks)	
	Late Miscarriage (20 to <28 weeks)	
Late miscarriage rate	All spontaneous abortion/miscarriage (non-therapeutic abortions) occurring between 20 to <28 weeks	All birth outcomes ≥20 weeks
Stillbirth rate	Stillbirth (≥28 weeks) and no signs of life	All live births and stillbirths ≥28 weeks
Perinatal mortality rate	Stillbirth + early neonatal death (birth to 7 days)	All live births and stillbirths ≥28 weeks
Neonatal mortality rate	Neonatal death (birth to 28 days)	Live births
Early onset sepsis	Very severe disease by current IMCI guidelines on any day in first week of life	Live births

#### Gestational age

The primary measure of gestational age is determined by maternal report of the first day of her LMP, reported during monthly pregnancy surveillance and with the aid of a prospectively completed menstrual calendar. An early ultrasound assessment (<20 weeks gestation) was originally planned for a random sample of 20 % of the enrolled women. In year 3 (2013), we began to conduct ultrasonography on as many enrolled pregnancies as possible.

#### Preterm live birth

Preterm live birth is defined as a baby born alive <37 weeks gestation defined by LMP. Early preterm live birth is defined as a baby born alive <34 weeks gestation defined by LMP. The denominator for preterm live birth rates is all live births.

#### Pregnancies with outcomes occurring prior to 37 weeks

This measure is defined as the spontaneous termination of pregnancy from 20 to <37 weeks resulting in: 1) preterm live birth, 2) late miscarriage (spontaneous pregnancy loss 20 to <28 weeks) that is not due to induced abortion, or 3) preterm stillbirth (28 to <37 weeks). A preterm stillbirth is defined as an infant born without signs of life (no spontaneous crying, breathing, and/or movement) at 28 to <37 weeks gestation. The denominator for this outcome is all births ≥20 weeks.

#### Clinically suspected early onset neonatal sepsis

Early onset neonatal sepsis is defined using the neonatal IMCI algorithm for very severe disease [52] with onset in the first week of life.

#### Small for gestational age

Small for gestational age is defined as birth weight <10 % (measured within the first 72 h of life) for gestational age using the INTERGROWTH-21 newborn birthweight standard [53].

#### Low birth weight

Low birth weight is defined as birth weight (measured within the first 72 h of life) of <2500 g. We will also assess the outcome of birth weight <2000 g.

#### Maternal morbidity

Maternal morbidity outcomes are assessed primarily by self-report. We follow maternal history for clinical signs indicating probable pyelonephritis and endometritis.

#### Neonatal mortality

In the event of death of a newborn during the neonatal period, the CHW refers the case to a supervisory staff member who conducts an in-depth verbal autopsy using a revised version of the WHO standard verbal autopsy instrument which has been used extensively by our study team and CHWs at the study site [54–56]. Verbal autopsy data are reviewed by two independent physicians, and a consensus on proximate and underlying cause(s) is reached. Data are further analyzed for cause-specific mortality using a computer-based expert algorithmic approach [57, 58].

### Sample size and analysis

In order to calculate the sample size, we first hypothesized that a population-level reduction in the preterm rate in the range of 15–20 % would be of public health importance, given the importance of the outcome and the level of complexity of any future scaled- up programmatic implementation of the intervention. Once we established this desired effect size range, we worked through a series of calculations (with corresponding assumptions) to determine the number of babies required to achieve sufficient power (i.e. 80 %) for a population-level reduction in this range (i.e. 15–20 %).

Given that the intervention is directed only at a subset of the population, we first estimated the proportion of preterm birth among both infected and non-infected women. Estimation of these proportions requires three parameters:The proportion of preterm in the population: we estimated this to be 20 %, based on our prior data from this population [51].The proportion of women in the intervention clusters that actually receive treatment under the universal screening program, or equivalently an estimate of the total proportion of women with UTI and/or AVF (Nugent ≥4).The ratio of preterm birth risk among infected and non-infected women; we estimated this ratio to be 2.5 from the literature.

From previous data and the literature, we estimated that about 15 % of women in this setting have either AVF, UTI, or both. Among those with AVF, some will fall into the intermediate flora score range (Nugent score 4–6) and some into the BV scoring range (Nugent score 7–10). Our best estimates of the relative proportions in these two subgroups was approximately 85 % within the BV (Nugent 7–10) range, with the remaining 15 % of women with AVF falling within the intermediate flora scoring range (Nugent 4–6) [24]. We based our prevalence estimates and treatment effect size on prior studies of similar screening and treatment programs for **all abnormal vaginal flora** (Nugent scores ≥4).

The last step in fixing our parameters and assumptions for sample size calculation was to examine the range of impacts that the intervention would need to afford ***among infected women*** in order to result in population-level impacts of 15 to 20 %. For a 50 % impact among infected women, we estimated a 15 % population-level reduction. For a 65 % impact on infected women, we estimated a 20 % population-level reduction. These impacts are consistent with those from prior studies that have demonstrated the impact of treatment of women with AVF (Nugent ≥4) is an approximately 60 % reduction in preterm births (Lamont et al.: 60 %, Ugwamadu et al.: 58 %). Assuming this impact (i.e. 60 %) among infected women to be similar to the impact in this population, the population-level effect size would be 18.4 %.

Having selected an effect size of 18.4 % (i.e. relative reduction in the population rate) we proceeded to estimate the sample size required. As the number of clusters available is fixed (*n* = 24), we followed an approach where first the sample size required under a naïve assumption of individual randomization was calculated, and then inflated by a factor (“design effect”) in order to account for correlation within CHW areas arising from the cluster-randomized design. We estimated this design effect as (1+ ***ρ*** •[ ***θ*** -1+ ***θ γ***^2^]), where ***ρ*** is the estimated intra-cluster correlation coefficient, ***θ*** is the mean sample size per cluster under individual randomization, and ***γ*** is the coefficient of variation in the cluster size [59]. Among ~16,000 births between June 2007 and September 2008 in this trial area, the intra-cluster correlation coefficient in this setting was 0.0060 (95 % CI: 0.0025–0.0095) and the coefficient of variation in cluster size was 0.33, leading to a design effect of 1.95 for preterm live birth. Taking this design effect into account, the number of live births required in each group to observe the estimated 18.4 % relative reduction with 80 % power and allowing 5 % Type I error is approximately 3367. Finally, we assumed that 90 % of the women screened at 13–19 weeks would have a live birth and 10 % would be lost to follow up, requiring enrollment of a total of 8314 in both control and intervention areas at the 13–19 week visit. Given a total population size of ~100,000 and a crude birth rate of 27/1000, we project that this sample will be reached in approximately 37 months, with total field work and follow-up of about 4 years.

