**Methods/Design:**

We are conducting a cluster randomized controlled trial that will enroll 10,000 pregnant women in Sylhet district in rural northeastern Bangladesh. Twenty-four clusters, each with ~4000 population (120 pregnant women/year) and served by a community health worker (CHW), are randomized to: 1) the control arm, which provides routine antenatal and postnatal home-based care, or 2) the intervention arm, which includes routine antenatal and postnatal home-based care plus screening and treatment of pregnant women between 13 and 19 weeks of gestation for abnormal vaginal flora (AVF) and urinary tract infection (UTI). CHWs conduct monthly pregnancy surveillance, make 2 antenatal and 4 postnatal home visits for all enrolled pregnant women and newborns, and refer mothers or newborns with symptoms of serious illness to the government sub-district hospital. In the intervention clusters, CHWs perform home-based screening of AVF and UTI. Self-collected vaginal swabs are plated on slides, which are Gram stained and Nugent scored. Women with AVF (Nugent score ≥4) are treated with oral clindamycin, rescreened and retreated, if needed, after 3 weeks. Urine culture is performed and UTI treated with nitrofurantoin. Repeat urine culture is performed after 1 week for test of cure. Gestational age is determined by maternal report of last menstrual period at study enrollment using prospectively completed study calendars, and in a subset by early (<20 week) ultrasound. CHWs prospectively collect data on all pregnancy outcomes, maternal and neonatal morbidity and mortality.

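### The design effect of 1.95 is computed at 144 births per cluster, but the trial will have 281; at the planning ICC the stated 80% power is about 60–64%

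*Protocol article*

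**What the plan says.** All of this is in the protocol article, section Sample size and analysis, unless another section is named.

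- For the baseline preterm proportion: "we estimated this to be 20 %, based on our prior data from this population".
- For the target effect: "Having selected an effect size of 18.4 % (i.e. relative reduction in the population rate").
- The number of clusters is fixed at 24, and the Randomization section allocates 12 to each arm.
- The design effect is 1 + ρ(θ − 1 + θγ²), where θ "is the mean sample size per cluster under individual randomization".
- The ICC is 0.0060 (95% CI 0.0025–0.0095) and the coefficient of variation of cluster size is 0.33, "leading to a design effect of 1.95 for preterm live birth". The source of these values is given as: "Among ~16,000 births between June 2007 and September 2008 in this trial area".
- The number of live births needed in each group "with 80 % power and allowing 5 % Type I error is approximately 3367".
- With 90% of screened women having a live birth and 10% lost to follow-up, this becomes 8314 women at the 13–19 week visit. The abstract describes a "cluster randomized controlled trial that will enroll 10,000 pregnant women".

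**The concern.** A design effect measures the loss of information in the trial that will be run, so its cluster size must be the one that trial will have. When clusters can be added, cluster size stays put and a single multiplication is right. Here the number of clusters is fixed, so every extra birth makes a cluster larger and raises the design effect again. The sample size has to be solved for cluster size; one multiplication stops too early.

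Power is the main operating characteristic of the design. If the trial finds no effect, readers will take the result as coming from a trial with a 20% chance of missing the planned reduction. If the true figure is nearer 36–40%, that reading is wrong. The article says the design was aimed at reductions of 15–20% as those of public health importance.

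**Working it through.** **Inputs** (section Sample size and analysis, and Randomization for the 12 per arm): p₁ = 0.20; relative reduction 18.4%, so p₂ = 0.20 × 0.816 = 0.1632; power 80%; type I error 5%, taken as two-sided because only the two-sided form reproduces the stated figure; 12 clusters per arm; ρ = 0.0060; γ = 0.33, so γ² = 0.1089.

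**1. Reproducing the plan.**
- Uninflated n per arm, two-sided comparison of proportions without continuity correction: 1722. Working back from the stated figures: 3367 / 1.95 = 1727.
- θ = 1722 / 12 = 143.5, or 1727 / 12 = 143.9.
- Design effect at 143.9: 1 + 0.006 × (143.9 − 1 + 143.9 × 0.1089) = 1.95, as stated.
- 1722 × 1.949 = 3356, within 0.3% of 3367. The one-sided form (2367) and the continuity-corrected form (3514) do not fit.
- Enrolment: 2 × 3367 / (0.9 × 0.9) = 8314, as stated.

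The published figures therefore follow from θ ≈ 144 and from nothing close to 281.

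**2. The cluster size the plan actually implies.** 3367 / 12 = 280.6 live births per cluster. The Study site and population section gives about 116 live births per cluster a year; over the projected 37 months that is 116 × 37 / 12 ≈ 358. A size of 144 does not match the recruitment plan either.

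**3. The same formula at θ = 280.6.**
- Design effect: 1 + 0.006 × (280.6 − 1 + 280.6 × 0.1089) = 2.86.
- Effective n per arm: 3367 / 2.86 = 1177.
- SE of the risk difference: √[(0.20 × 0.80 + 0.1632 × 0.8368) / 1177] = 0.01587.
- Difference / SE: 0.0368 / 0.01587 = 2.318.
- Normal power: Φ(2.318 − 1.960) = 0.64.
- Noncentral t with 24 − 2 = 22 df: 0.60.

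**4. Sensitivity.**

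| Scenario | Power, normal | Power, t (22 df) |
|---|---|---|
| 3367 per arm, ICC 0.0025 | 84% | 80% |
| 3367 per arm, ICC 0.0060 | 64% | 60% |
| 3367 per arm, ICC 0.0095 | 50% | 47% |
| 3367 per arm, ICC 0.0060, equal clusters (γ = 0) | 67% | 63% |
| 4050 per arm, ICC 0.0060 | 67% | 63% |

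The 4050 is 10,000 × 0.81 / 2. It applies the article's 81% yield to the abstract's 10,000; this is an assumption, because the article defines that yield for women seen at 13–19 weeks.

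**5. Detectable reduction at 80% power** (3367 per arm, ICC 0.0060): about 22% (normal) or 23% (t).

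**6. Can more births restore 80%?** As cluster size grows, effective n per arm approaches 12 / (0.006 × 1.1089) ≈ 1804, which gives about 82% power (normal) or 78% (t). The required n per arm is n_ind × 0.994 / (1 − n_ind × 0.006 × 1.1089 / 12). With n_ind = 1722 this is about 37,800; with 1727 it is about 40,400. The result is unstable because it lies near the limit. On the t basis no number of births is enough.

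**7. Source of the ICC.** The article's own population and crude birth rate give 100,000 × 27/1000 × 16/12 = 3,600 births in the 16 months from June 2007 to September 2008, not about 16,000.

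**The case against.** The recalculation itself is not in dispute. The case against concerns its reach.

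- **The 60–64% holds only at the ICC point estimate.** This stands as a qualification. The article's interval for the ICC includes values at which power reaches 80%, but only near its lower end: about 0.0031 on the normal approximation and 0.0025 on the t. The article plans at 0.0060, so its 80% must be judged there.
- **The abstract's 10,000 women exceed 8314.** The two numbers need not conflict: 8314 is counted at the 13–19 week visit, and enrolment can start at 5 weeks. But the larger number does not rescue the power, which is 67% / 63% if all 10,000 are given the 81% yield.
- **Restricted randomisation on predicted preterm births may recover precision.** It may, but the sample-size section takes no credit for it, and the first set of models is unadjusted.
- **The final analysis is unaffected.** True: confidence intervals will allow for clustering through GEE and will show the precision achieved. Both interim reviews are also past. This limits the harm to how the design is described and how a null result is read; it does not make the stated power right.
- **The 16,000 births may be loose wording.** Possibly. Nothing shows that the ICC or the coefficient of variation is wrong, and the power result does not depend on this point.

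**Conclusion.** The statement is wrong as written. The article defines the design effect at a cluster size the trial will not have, and its formula and its resulting sample size contradict each other. On its own inputs the design effect is 2.86 rather than 1.95, the effective sample is 1177 rather than 1727 per arm, and power for an 18.4% reduction is 64% (normal) or 60% (t, 22 df). The chance of missing the planned effect is therefore 36–40%, and the detectable reduction of 22–23% lies above the whole 15–20% target range.

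This rests on ICC 0.0060, CV 0.33, a 20% control proportion, a two-sided 5% test, and no precision gained from the restricted randomisation. With 24 clusters and this ICC, 80% power for the planned effect is practically out of reach. The birth count given as the source of the ICC is a smaller, separate inconsistency. It leaves unclear whether the ICC and CV describe these 24 clusters.

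**What to change.** In the section Sample size and analysis:

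1. Define θ as the expected number of live births per cluster in the trial (281) and replace 1.95 with 2.86.
2. Restate power for an 18.4% reduction at 3367 live births per arm as about 64% (60% on 22 df), or give the reduction detectable with 80% power as about 22–23%.
3. Show power over the ICC interval: 84% to 50% (normal), 80% to 47% (t).
4. Correct or explain the statement about 16,000 births. Re-estimate the ICC and the cluster-size CV on the 24 trial clusters from the prior data already used for the restricted randomisation, and update items 1–3 if the values change.

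No added enrolment is proposed, since more women in the same clusters barely raises power. The cost is a rewritten paragraph, a small re-analysis of existing data, and a less favourable stated power.
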